### 3. Hypothesis

The comparison of the mean INR between branded and generic warfarins is within the limit of 0.49 (two-sided, with a significance level of 5%) demonstrating therapeutic equivalence between them.

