#### **4.3.2 Exclusion criteria**

Patients who meet any of the following criteria will not be accepted:

- patients to whom the use of anticoagulants is contraindicated (patients using other anticoagulants, or with active bleeding, or with hypersensitivity to warfarin, or with ulcers);
- women of childbearing age, or who are pregnant or breastfeeding;
- patients with thrombocytopenia;
- patients with liver or kidney failure;
- patients with a history of bleeding episodes due to congenital deficiency of coagulation factors;
- patients enrolled in other clinical trials;
- patients not reaching a TTR of at least 70% in the first phase of the study (will be considered non-adherent to therapy);
- patients starting treatment with drugs that are contraindicated or that incur in moderate or major interactions when used concomitantly with warfarin, according to the online database Micromedex 2.0 (37) (Annex II).

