##### **4.5.2 Secondary outcomes**

- Mean PT

The mean PT will be evaluated in the same way as the INR.

- Time within the therapeutic range (TTR).

This ratio is calculated for each patient by the percentage of person-time within the therapeutic range of 2.0 and 3.0 divided by the total person-time contribution by that same individual (39).

- Frequency of thromboembolic events

It includes ischemic stroke (differentiated from hemorrhagic stroke by tomography) and thromboembolism on the viscera or extremities (diagnosed by acute symptoms and relevant diagnostic tests) (40).

- Frequency of bleedings

Bleeding events will be classified as major or minor bleedings:

- Major bleeding: intracranial bleeding, fatal bleeding, blood loss resulting in a decrease greater than or equal to 2.0 g / L of serum hemoglobin, bleeding requiring transfusion, bleeding in sensitive areas such as the retina or pericardium.
- Minor bleeding: all other bleeding (33).

- Adherence to treatment

Adherence will be calculated by the amount of tablets returned by the patient.

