##### **4.6.2 Statistical analysis**

All statistical analyzes will have a significance level of 5%. Paired-samples t-tests (also called dependent T-tests) will be used for the outcome of mean INR and PT. Analysis will be performed by protocol for these outcomes i.e., data from patients who start treatment with any drugs that interact with warfarin as previously defined (list in Annex II) will be excluded from the final analysis.

The dichotomous outcomes (TTR, thromboembolic events, bleeding) will be analyzed by McNemar's test. Exploratory analyzes for patient subgroups are not planned. The dichotomous variables will be analyzed by intention to treat, considering the missing data as an unfavorable outcome, in which case a sensitivity analysis will be carried out to assess the robustness of the result.

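### TTR is defined as a percentage per patient but is analysed as a yes/no outcome by McNemar's test, with no cut-off stated

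*Protocol*

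**What the plan says.** Protocol Section 4.5.2 (Secondary outcomes) gives the definition: "This ratio is calculated for each patient by the percentage of person-time within the therapeutic range of 2.0 and 3.0", divided by the total person-time that the patient contributed. The result is a number from 0 to 100 for each patient.

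Section 4.6.2 (Statistical analysis) assigns the test: "The dichotomous outcomes (TTR, thromboembolic events, bleeding) will be analyzed by" McNemar's test. It adds that dichotomous variables are analysed by intention to treat, "considering the missing data as an unfavorable outcome", with a sensitivity analysis.

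The same section plans paired t-tests, which "will be used for the outcome of mean INR and PT", on a per-protocol set.

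The only TTR threshold in the protocol is in Section 4.3.2 (Exclusion criteria), which removes "patients not reaching a TTR of at least 70% in the first phase of the study" as non-adherent.

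**The concern.** McNemar's test compares paired yes/no values and uses only the pairs that disagree. A percentage has to be cut before the test can be applied, and the protocol names no cut for the outcome. Three things follow.

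- **The analysis cannot be run as written.** A cut chosen later leaves a freedom that can change the result, and it could be chosen after seeing data.
- **The label sets more than the test.** It also puts TTR in the intention-to-treat set and gives it a missing-data rule that presupposes a yes/no result. Mean INR, built from the same INR readings, is analysed per protocol.
- **A cut usually lowers sensitivity.** The trial seeks to show equivalence, so a non-significant result from a weaker test could be taken as reassurance about INR control.

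**Working it through.** **1. The text.** Section 4.5.2 gives a continuous value. Section 4.6.2 gives a label, a test and a missing-data rule that all need a binary value. Section 4.3.2 gives a threshold, but it decides who stays in the trial after phase one and is not tied to the outcome. Nothing joins these. This step needs no outside figure.

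**2. The plan's own figure.** Section 4.6.1 uses a difference of 0.49, SD 0.29, two-sided 5% and 90% power:

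n per group = 2 × (1.960 + 1.282)² × 0.29² / 0.49² = 2 × 10.51 × 0.0841 / 0.2401 = 7.36, rounded up to 8; 8 × 6 = 48.

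The stated 48 is reproduced. It rests on mean INR, so TTR does not enter it.

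**3. What a cut does, by hand.** Take a 28-day phase and, for illustration, a 70% cut (19.6 days).
- 28 days in range on one product and 21 on another is 100% against 75%. Both are yes, so McNemar's test ignores a 7-day difference.
- 20 days against 19 days is 71.4% against 67.9%. This is a full yes/no disagreement for a 1-day difference.

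**4. Power when TTR is simulated directly.** All TTR inputs are assumed: mean 70 or 80, SD 20 to 30, within-patient correlation 0.3 or 0.5, values clipped to 0–100, and N = 48 or 60. The true difference is set for about 90% paired-t power before clipping. For N = 60, SD 20 and correlation 0.3:

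SD of the difference = 20 × √(2 × 0.7) = 23.7; difference = 3.24 × 23.7 / √60 = 9.9 points.

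With mean 80, the paired t-test then has power 0.87. McNemar's test at a 70% cut has 0.56 (exact) or 0.65 (uncorrected chi-square). Over all settings:

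| Analysis | Power |
|---|---|
| Paired t-test on the percentage | 0.84–0.88 |
| McNemar, cut 60% or 70%, exact | 0.36–0.58 |
| McNemar, cut 60% or 70%, uncorrected | 0.46–0.67 |
| McNemar, cut 100%, exact | 0.03–0.41 |
| McNemar, cut 100%, uncorrected | 0.15–0.50 |

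**5. Power when TTR is built from INR readings.** Mean INR is 2.45 (Section 4.6.1). Each phase has 3 or 5 readings with linear interpolation between them: Section 4.5 says tests are twice a month, while Section 4.4 speaks of weekly measurements. Assumed SDs are 0.2 between and 0.4 within patients, or 0.29 and 0.5. The formulations differ either in INR level (0.3 or 0.4) or in variability (within-patient SD × 1.6). Selected results:

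| N, readings, SDs | Difference | Paired t | McNemar 70%, exact / uncorrected |
|---|---|---|---|
| 48, 5, 0.29/0.5 | level 0.4 | 0.88 | 0.48 / 0.58 |
| 48, 3, 0.2/0.4 | level 0.3 | 0.81 | 0.54 / 0.63 |
| 60, 3, 0.29/0.5 | variability | 0.86 | 0.79 / 0.84 |

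The largest loss is 0.88 − 0.48 = 40 points and the smallest is 0.86 − 0.84 = 2 points. Across all scenarios with paired-t power of 0.7 to 0.95 and a 60% or 70% cut, the loss is about 7 to 40 points (exact) or 2 to 30 points (uncorrected).

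**6. Dependence on the cut.** In the first row of that table, exact McNemar power is 0.63 at a 60% cut, 0.48 at 70% and 0.06 at 100%.

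**The case against.** The strongest reply is that McNemar's test on a dichotomised TTR is a valid paired test. Section 4.6.2 does declare TTR dichotomous, 70% is a natural level of adequate control, and a responder cut is a detail often left to an SAP, which may exist. Part of this stands: a prespecified cut would make the test legitimate, and the choice would then be one of efficiency. It does not remove the point. The protocol is not silent here; it states a variable type that conflicts with its own definition. An SAP could settle that only by overriding one of the two sections or by adding a cut that the protocol lacks.

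Several stronger readings are tempting and are not supported:

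- *A large share of power is certainly lost.* The protocol gives no SD, correlation, effect or cut for TTR. The loss can be as small as 2 points. The INR-based simulation also ignores dose adjustment (Section 4.4.2) and the selection on phase-one TTR (Section 4.3.2).
- *A loss of INR control would be missed by the trial.* Not if it is a shift in mean INR. Take a shift of 0.4, 48 patients, visit SD 0.45 and 2 readings per phase with independent errors. The SD of the difference is √(2 × 0.45² / 2) = 0.45 and the noncentrality is 0.4 × √48 / 0.45 = 6.2. The primary paired t-test then has power above 99.9%. TTR adds most beyond the mean when products differ in variability, which is where the loss is smallest.
- *TTR is the secondary outcome closest to clinical benefit.* Section 4.5.2 lists thromboembolic events and bleeding, which are the clinical outcomes themselves.
- *The 70% is the intended outcome cut.* Section 4.3.2 uses it only for exclusion.

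**Conclusion.** The concern holds as an inconsistency in the plan for one secondary outcome. Sections 4.5.2 and 4.6.2 disagree on the scale of TTR, and McNemar's test cannot be applied to TTR as defined without a cut that the protocol does not give. This rests on the text alone.

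The cost in power is typically substantial but depends on assumptions. It is about 2 to 40 points in the INR-based simulation at a 60% or 70% cut, least when formulations differ mainly in INR variability and most when they differ in INR level.

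A reader might infer that the trial's main conclusion or its size is in doubt. It is not: the analysis of mean INR and the 48 patients do not depend on how TTR is tested.

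**What to change.** In Section 4.6.2:

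- Remove TTR from the list of dichotomous outcomes.
- Analyse the TTR percentage for each phase as a paired continuous outcome: a paired t-test as for INR and PT, a signed-rank test if the differences are strongly skewed, or a crossover model with period. Report the mean difference with a confidence interval.
- Name the analysis set for TTR, since leaving the dichotomous group also removes the intention-to-treat rule.
- Replace the missing-equals-unfavorable rule for TTR with one suited to a percentage. Section 4.5.2 already divides by the person-time contributed, so a partly observed phase can still give a value. The rule must say what happens when a phase has no usable INR interval.
- Show any 70% cut only as a prespecified descriptive summary.

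Stating a cut in advance and keeping McNemar's test would also reconcile the two sections, but it accepts the loss of power. Either way the cost is a few sentences, settled before unblinding, with no new data, visits or patients.

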#### **4.6 Statistical Method**

##### **4.6.1 Sample size**

At least 48 patients (8 in each group) will be needed in order to identify a clinically significant difference of 0.49 in the INR, considering a mean INR of 2.45 with standard deviation of 0.29, data reported for a branded warfarin in a published study (13). The sample was calculated based on the mean INR outcome, using the statistical method for quantitative outcomes (41) assuming  $\alpha = 5\%$  and  $\beta = 10\%$ , which result in a power of 90%. We plan to recruit 60 individuals (10 in each group) to compensate for possible dropouts or exclusions of patients.

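### Scoring missing data as an unfavourable outcome in the main analysis makes each lost phase a thromboembolic event and a bleed; for thromboembolism the imputed events would outweigh the real ones

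*Protocol*

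**What the plan says.** Protocol section 4.6.2 names the outcomes and the test: "The dichotomous outcomes (TTR, thromboembolic events, bleeding) will be analyzed by McNemar's test". It then sets the analysis population and the rule for missing data: "The dichotomous variables will be analyzed by intention to treat, considering the missing data as an unfavorable outcome". The same sentence adds "in which case a sensitivity analysis will be carried out to assess the robustness of the result", without saying what that analysis will be.

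Two other places show that missing phases are expected. Section 4.6.1 says: "We plan to recruit 60 individuals (10 in each group) to compensate for possible dropouts or exclusions of patients", against a stated need of 48. Section 4.3.2 excludes "patients not reaching a TTR of at least 70% in the first phase of the study". Under section 4.4, patients already take their randomised product in phase one, so this exclusion acts after randomisation.

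Section 4.5.2 lists both event outcomes as secondary and counts every bleed that is not major as a minor bleed. The protocol gives no expected rate for either outcome.

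**The concern.** For a success-type outcome, scoring missing as unfavourable means scoring it as a failure, which is a familiar cautious rule. For thromboembolism and bleeding, the only unfavourable value is that the event happened. A patient who leaves the trial well is then recorded as having had a thromboembolic event and a bleed in every phase not observed.

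Two things are at stake.

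- **The reported frequencies.** If real events are rare, the counts mainly show how many patients left.
- **The comparison.** The trial aims to show that the formulations are equivalent. Adding similar numbers of imputed events to each one pulls their frequencies together. Worst-case scoring is therefore not conservative here, although it often is in a superiority trial.

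**Working it through.** **Inputs from the protocol.** 60 recruited and 48 needed (4.6.1); three formulations, each evaluated over one 28-day phase (4.4); six treatment sequences of equal size (4.1, 4.6.1).

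**Assumptions.** Thromboembolic rate 1% to 5% per year. Missingness is counted by phase. McNemar's test is applied to each pair of formulations. When losses are spread evenly, a lost patient is equally likely to leave before phase 2, 3 or 4.

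**1. The plan's own figure.** With difference 0.49, SD 0.29, two-sided 5% and 90% power, n per group = 2 × (1.960 + 1.282)² × 0.29² / 0.49² = 7.4, rounded up to 8. Six groups give 48, and 48 / 0.8 = 60. The stated figures reproduce, and the implied allowance is 60 − 48 = 12 patients (20%).

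**2. Real thromboembolic events.** Per formulation: 60 × 28 / 365.25 = 4.60 patient-years.

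| Assumed rate per year | Real events per formulation | Over three formulations |
|---|---|---|
| 1% | 0.05 | 0.14 |
| 2% | 0.09 | 0.28 |
| 5% | 0.23 | 0.69 |
| 10% | 0.46 | 1.38 |

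A single patient missing a single phase adds 1 imputed event. That exceeds the expected real total over all three formulations at every rate from 1% to 5%.

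**3. The planned allowance.**

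- All 12 lost before phase 2: each formulation gets 12 imputed events, 12 / 60 = 20%. At 5% per year the imputed share is 12 / (12 + 0.23) = 98%, and it is higher at lower rates.
- Losses spread evenly: a lost patient misses 3, 2 or 1 phases, 2 on average, so 12 × 2 = 24 imputed phase-level events.

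**4. McNemar's test.** A patient lost before phase 2 has an imputed event on all three formulations, so is concordant in every comparison and adds nothing to the test. A patient lost before phase 3 or phase 4 is discordant in two of the three comparisons and concordant in the third. Each such pair counts against the formulation scheduled later.

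- Imputed discordant pairs per comparison, 12 losses spread evenly: 12 × 2/3 × 2/3 = 5.3.
- Other discordant pairs, from 48 completers with 28-day risk p: 48 × 2 × p × (1 − p). With p = 0.00077 (1% per year) this is 0.07; with p = 0.00383 (5% per year) it is 0.37. A simulation of 3,000 trials gave 0.08 and 0.34.
- False positives: with loss unrelated to formulation and balanced sequences, an imputed discordant pair falls either way with equal chance. In the simulation, exact p fell below 0.05 in about 1% of comparisons (0.9% to 1.4%), under the nominal 5%.

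**5. Bleeding, major plus minor.** There are 60 × 3 = 180 patient-phases. Imputed events equal real ones when the share of patients bleeding per phase is:

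- 12 losses spread evenly: 24 / (180 − 24) = 15%;
- 3 losses spread evenly: 6 / (180 − 6) = 3.4%.

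Below the break-even share, imputed bleeds outnumber real ones; above it, they do not.

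**6. Frequencies pulled together (illustration).** Take 0 against 3 real bleeds among 48 completers, 0% against 6.3%. With 12 patients lost before phase 2, this becomes 12 against 15 of 60, 20% against 25%, a ratio of 1.25. McNemar's test is unchanged, because the added pairs are concordant; only the reported frequencies move.

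**The case against.** The best defence is that the same sentence plans a sensitivity analysis, the outcomes are secondary, and the primary mean INR analysis is per protocol and untouched. All of that is true. It lowers the weight of the point but does not answer it, because the main result for the two safety outcomes still rests on the rule.

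A reader might also infer more than the protocol supports:

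- **A false safety signal.** Six discordant pairs all in one direction give an exact p of 0.031 with no real event. That is a hand-picked extreme. With balanced sequences and loss unrelated to formulation, the test stays below its nominal level, and five pairs in one direction give only p = 0.0625. What stands is that the test carries almost no information about thromboembolism.
- **Imputed bleeds always swamp real ones.** This does not follow. Minor bleeds count, no bleeding rate is given, and with few losses and common minor bleeding the real events are the larger number.
- **Every patient who starts an Annex II drug counts as an event.** Section 4.6.2 drops their data from the INR and PT analyses only. It does not say that event follow-up ends, so their event data need not be missing.
- **Every phase-one TTR failure counts as an event.** These patients have been randomised, so intention to treat in its usual sense includes them. The protocol does not say so expressly, nor whether their follow-up stops.
- **Observed counts will be withheld.** The protocol does not say this. They may be shown, but they are not the planned main analysis.

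**Conclusion.** The point holds as a fault in the main analysis of two secondary outcomes. For thromboembolism it is firm: at 1% to 5% per year, one lost patient already outweighs the expected real events, and at 10% per year (1.38 events in all) the 12-patient allowance still dominates. For bleeding, the frequencies are distorted whenever phases are missing, but whether imputed events are the majority is conditional on the break-even shares above.

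The event rates, the number lost and the timing of loss are assumptions; 12 is the planned allowance and not a forecast. The harm is reported frequencies that cannot be interpreted and formulations that look more alike than the data show. An inflated false-positive rate is not part of the finding.

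**What to change.** In section 4.6.2, for thromboembolic events and bleeding:

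- make observed events, attributed to the formulation being taken, the main analysis, with the number at risk or patient-days and exact confidence intervals per formulation;
- keep McNemar's test, on patients observed in both compared phases;
- report losses by formulation and phase;
- keep missing-as-event only as the extreme case in the sensitivity analysis already planned, and say so.

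The cost is a short rewrite of one paragraph, with no extra data. The observed-event analysis assumes that loss is unrelated to events. The retained extreme case shows how far the result depends on that.

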## ANNEX II

List of warfarin sodium interactions with drugs and food, according to severity (unknown, minor, moderate, major or contraindicated). DrugPoint Summary (42)

### Contraindicated

Tamoxifen citrate

### Major

|                        |                        |                         |                   |                             |               |
|------------------------|------------------------|-------------------------|-------------------|-----------------------------|---------------|
| abciximab              | cephalothin sodium     | enzalutamide            | leflunomide       | Papaya                      | teriflunomide |
| acenocumarol           | cephapirin             | eptifibatide            | lepirudin         | paroxetine                  | testosterone  |
| alefacept              | cephradine             | erlotinib               | levofloxacin      | penicillin G                | ticarcillin   |
| amiodarone             | Chamomile              | erythromycin acistrate  | lomitapide        | penicillin V benzathine     | ticlopidine   |
| amoxicillin            | ciprofloxacin          | escitalopram            | Lycium            | pentosan polysulfate sodium | tinzaparin    |
| ampicillin trihydrate  | citalopram             | etoposide               | Marijuana         | phenindione                 | tirofiban     |
| apixaban               | clarithromycin         | etravirine              | mechlorethamine   | phenprocoumon               | torsemide     |
| aprepitant             | clopidogrel            | fenofibrate             | methicillin       | piperacillin                | valproic acid |
| aspirin                | cloxacillin benzathine | fenofibric acid         | methotrexate      | Pomegranate                 | venlafaxine   |
| azythromycin           | Cranberry juice        | fibrinolytic agents     | Methyl salicylate | posaconazole                | vilazodone    |
| bivalirudin            | cyclophosphamide       | Fish oil                | metronidazole     | prasugrel                   | vincristine   |
| capecitabine           | dabigatran             | fluconazole             | miconazole        | procarbazine                | vindesine     |
| carbenicillin disodium | dabrafenib             | fluoruracil             | milnacipran       | proguanil                   | voriconazole  |
| carboplatin            | dalteparin             | fluoxetine              | moxalactam        | rivaroxaban                 |               |
| cefadroxil             | danaparoid             | fluvoxamine             | moxifloxacin      | ropinirole                  |               |
| cefdinir               | dapsone                | Garlic                  | nafcillin         | roxithromycin               |               |
| cefepime               | deferasirox            | gatifloxacin            | nalidixic acid    | sertraline                  |               |
| cefixime               | desvenlafaxine         | gemifloxacin            | nandrolone        | simvastatin                 |               |
| cefotaxime             | dicloxacillin          | Ginkgo biloba           | naproxen          | sitaxsentan                 |               |
| cefpodoxime            | dipyridamole           | imatinib                | norfloxacin       | St John's Wort              |               |
| ceftazidime            | doxorubicin            | infliximab              | noscipine         | sulfafurazol                |               |
| ceftibuten             | dronedarone            | Influenza virus vaccine | ofloxacin         | sulfamethoxazole            |               |
| ceftizoxime            | Drotrecogin alfa       | itraconazole            | oseltamivir       | sulfisoxazole               |               |
| celecoxib              | enoxacin               | ketoconazole            | oxacillin         | Tan shen                    |               |
| cephalexin             | enoxaparin             | ketoprofen              | oxandrolone       | telithromycin               |               |

